| **Notes** | -First microtrial to be conducted  -Incentive given after completion of IVR survey (Post-IVR) | -Incentive amount will range from X to 2X | -1:20 odds of winning lottery; incentive is 5 times amount in fixed incentive arm | -Provide same incentive in each arm  -The only difference in the questionnaire is the survey’s introduction. | -Human intro is a call center that asks participants if they wants to participate and if so, patches them into an IVR  -Provide same incentive in each arm | -Incentive and survey introduction used are top performers from microtrials #1-4 | - IVR arm will receive IVR survey first, followed by CATI survey 7 days later  -- CATI arm will receive a CATI first followed by an IVR survey 7 days later. |

Abbreviations: CON, contact rate; MNO, mobile network operator; RR, response rate, COMP, completion rate; R, refusal rate

***2. Describe the number and type of study visits and/or contacts between the study team and the participant, how long they will last, and where/how they will take place.***

There will be no face-to-face (i.e. in-person) contact between participants and the study staff. All interactions with research participants will be through the participant’s personal mobile phone. Participants will be randomly selected from a list of randomly generated mobile phone numbers (microtrials 1-5) or from a pre-defined and de-identified list of mobile numbers provided by a MNO or household survey. The selected mobile phone number will be sent one text message that alerts the potential participant about the upcoming survey. For all *microtrials* except for *microtrial #7,* participants will be sent one MPS. If a participant decides to answer the MPS, the time to complete the survey should be no more than 30 minutes. For *microtrial #7*, participants will be sent a CATI and IVR survey separated by seven days. In a sub-sample of participants who either refused to participate in the IVR survey, did not initiate the survey, or who did not complete the survey, participants will be called back by a human operator to understand reasons for their not fully participating in the survey. This interview is expected to take no more than 30 minutes. Therefore, participants may have up to three contacts with the mobile phone survey. For each contact, a verbal consent will be taken.

***3. Describe the expected duration of the study from the perspective of the individual participant and duration overall.***

A MPS is expected to take no more than 30 minutes. Within one week of being sent an MPS, a sub-sample of participants may be called back by a human operator to understand reasons why they did not fully participate in the survey. Therefore for microtrials #1-6, the potential length of duration would be one week with up to two study contacts. For *microtrial* #7, participants will be sent two surveys spaced seven days apart. Following the second survey, a sub-sample of participants may be called back to understand reasons why they did not fully participate in the survey. Therefore, for *microtrial #7* the potential length of duration would be two weeks with up to three study contacts.

***4. Provide a brief data analysis* plan *and a description of variables to be derived.***

The contact rates, response rates, and completion rates will be tabulated for each of the microtrials by study arm; where contact, response, and completion rates are defined as:

The contact, response, and completion proportions^[[1]](#footnote-1)^ will be tabulated for each of the *microtrials* and by study arm where contact, response, and completion are defined as:

$$Contact Rate= \frac{CI+PI+R}{CI+PI+R+(NC+U)}$$

$$Response Rate= \frac{CI+PI}{CI+PI+R+NC}$$

$$Completion rate= \frac{\mathrm{CI}}{CI+PI+R}$$

**CI** (Complete Interview): a respondent that answered all applicable questions

**PI** (Partial interview): a respondent who consented to the survey but did not answer all questions

**R** (Refusal): a respondent who: 1) did not consent to the survey, or 2) formally withdrew during the survey

**NC** (Non-contact): a working phone number where the respondent picked up but did not engage with the survey. This is assessed by looking at the system log for time spent on the survey

**U** (Unknown): a phone number that cannot be determined whether it is a working phone number (the respondent did not pick up the phone) or not (the phone number is not eligible)

Respondents who report being less than 18 years old are considered ineligible. Ineligible respondents are excluded from the equations for contact, response, and completion rates.

Contact, response, and completion proportions will be compared by study arm for each microtrial and by incentive group. *A priori, a*n alpha of 0.05 will be used for hypothesis testing.

Partially completed surveys will be tabulated and stratified by both the question number, and the question content due to the randomization of NCD topic modules. Additionally, the average time spent answering, the number of “Don’t know” or “Refuse to answer” responses, and the number of times the question was repeated will be calculated for both the chronological question number and question content and stratified by study arm. For microtrial #7, test for agreement in survey responses between the survey modalities will be assessed using Cohen’s Kappa.

In microtrial #7, participants will be asked to answer two surveys (IVR and call center [CATI]) composed of the same questions so that question validity can be assessed. For example, analyses will be conducted to observe whether some people may be more likely to report unhealthy habits when taking the automated IVR survey as compared to a call center because the human element is removed in an IVR survey.

Risk factor data will be collected and stored from other microtrials. This data will be compared to publically available results and national estimates to help determine if the protocol’s mobile-collected risk factor’s prevalence are similar to national estimates of household collected data. This will help answer whether the protocol’s mobile phone sample is as healthy, or unhealthy, as the traditionally administered surveys.

*5.*  ***Describe whether you are collecting or storing personal identifiers, and if yes, why you need them, and when and how you plan to dispose of them. Signatures on consent forms are considered to be identifiers.***

We will not collect personal identifiers via the consent process. Mobile phone numbers that were randomly generated are the personal identifiers. Because of the nature of the trial, the mobile phone numbers are needed to generate data. While phone numbers will initially be logged in the VOTOmobile platform alongside the data collected, immediately after each microtrial has been completed, the PI will download the database from the VOTOmobile platform and permanently delete the column containing mobile phone numbers. Phone numbers need not be retained for purposes of the study. No other potentially individually identifying data will be collected.

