We are requesting a modification to written signed informed consent due to the nature of the research activities. Potential participants are unable to provide written informed consent as there is no face-to-face interaction. Moreover, as is common practice for brief IVR and CATI surveys, an abbreviated standardized verbal disclosure of key study information noting the voluntary nature of the survey will precede any data collection. After a brief introduction and opportunity for potential respondents to select their preferred language, potential participants will be read a brief description of the study and expected time burden in their language of choice. Potential participants will then be asked to “Press 1” if they would like to continue with the study. Individuals who do not “Press 1” will have the survey terminated. For participants in microtrial #5 and #7 where CATI surveys are conducted, the human operator will not proceed without a voluntary affirmative statement indicating the individual’s willingness to participate after he/she hears about the study.

*2.* ***Identify the countries where the research will take place, and the languages that will be used for the consent process.***

This study will be conducted in four of the following countries: Bangladesh, Lebanon, Kenya, Tanzania, Uganda, and Ghana. The consent/disclosure statement in the IVR survey will be made available in the most common languages for that study area. The statement will be translated into local languages and back-translated into English to ensure accuracy.

C. Study Implementation:

*1.* ***Describe the procedures that participants will undergo. If complex, insert a table below to help the reviewer navigate.***

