After the language selection, the speaker will provide a more detailed description of the study which includes the purpose, duration, risks, benefits, and the sponsoring agency. If incentives are not prohibited in the country, participants will also be told about requirements to receive an incentive and the incentive amount. Potential respondents will be asked a demographic screening question. Respondents will be screened on age; those who indicate being less than 18 years old will be thanked for their interest and the survey will be terminated. If screening criteria are met, respondents will then be asked whether they agree to participate in the study (consent). Respondents who choose to continue with the survey - after hearing about its purpose, procedures and voluntary nature - will be asked to press a number on their keypad to indicate their willingness to continue (e.g. “Press 1 if you would like to participate in this survey. Press 3 if you do not want to participate in the survey”). Participants will be asked again to confirm their participation (e.g. “You have indicated that you do wish to complete the survey, press 1 to continue the survey or press 3 to end this survey”) to ensure that consent (or refusal) was not mistakenly provided. Respondents who do not agree to participate, will be thanked for their time and the survey will end. Following consent, respondents will receive and answer a series of NCD modules whose order of presentation is randomized as described above.

At any time after the MPS has been initiated (i.e. participants met screening criteria, consented, and began answering NCD topical questions) participants will be able to formally opt-out of survey participation by pressing a sequence of buttons on their mobile phone (The precise combination of buttons will be determined by in-country programming and implementation teams). NCD surveys will only be sent to participants once; that is participants who were ineligible due to screening criteria, refused consent, or formally opted out during the survey will not have an additional NCD survey sent.

The MPS will be delivered at random times ranging from 8:00am to 8:00pm local time. The exact time window to deliver the notification SMS and MPS will be determined by each country during the FGD (JHU IRB No: 0000709).

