This microtrial seeks to examine whether the survey introduction’s modality (human operator versus those who receive an IVR survey introduction) has an effect on survey response and completion rates. Participants will be randomized to one of two arms: 1) a human will call the RDD-generated mobile phone number and read the survey’s introduction. The operator will answer any questions the participant may have, consent the participant and then patch the participant into the IVR survey, and 2) the participant will receive a IVR survey with a survey introduction in IVR format and similar to the previous *microtrials*.

Objective 3: Evaluation of the Sampling Frame

*Microtrial #6*- Evaluation of the sampling frame of mobile phone numbers

This microtrial seeks to examine whether the source of the mobile phone numbers has a differential effect on the IVR survey’s response and completion rates. The previous five *microtrials* relied on a RDD sampling frame. In this microtrial, we will obtain a de-identified list of mobile phone numbers from either a mobile network operator or from a previously conducted household survey where participants had consented to be contacted for additional studies. Participants will be sent an IVR survey with the top performing survey introduction (results from microtrials 4 and 5) and the top performing incentive (microtrials 1-3).

Objective 4: Evaluation of Survey Modality

*Microtrial #7*- Evaluation of CATI and IVR survey metrics

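### In microtrial 5 the response rate counts spoken consent in one arm and confirmed keypad consent in the other, so people lost on first meeting the IVR count as responders only after a human introduction

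*Protocol*

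**What the plan says.** The data analysis plan (Study Procedures, section C.4) puts complete and partial interviews in the response numerator, over CI+PI+R+NC. Completion is CI/(CI+PI+R). A partial interview is "a respondent who consented to the survey but did not answer all questions". A person who declined consent, or who "formally withdrew during the survey", is R. A person who picked up but did not engage is NC. These proportions are compared by arm at alpha 0.05.

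Microtrial 5 (Microtrial Designs) compares a human with an IVR introduction on response and completion.

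- **Human arm.** The operator will "consent the participant and then patch the participant into the IVR survey". The Consent Process section adds, for microtrials 5 and 7, that "the human operator will not proceed without a voluntary affirmative statement".
- **IVR arm.** Here "the participant will receive a IVR survey with a survey introduction in IVR format and similar to the previous" microtrials, so the standard flow applies. Under Survey Delivery, willing respondents "will be asked to press a number on their keypad to indicate their willingness to continue", and then "Participants will be asked again to confirm their participation".

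Survey Delivery also describes an initiated survey as one where "participants met screening criteria, consented, and began answering NCD topical questions".

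**The concern.** Consent is the event that turns a contact into a responder, and in microtrial 5 it sits on opposite sides of the first encounter with the automated system. The human arm has an extra exit after consent: hanging up when the recording starts, a failed transfer, or being unable to use the keypad. Anyone who leaves there without formally opting out is PI. In the IVR arm the same difficulties arise before consent, so the same person never becomes PI.

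Response is one of the two outcomes named in microtrial 5's stated question. If it can rise with no additional survey data, it cannot show by itself that a human introduction brings more people into the survey.

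**Working it through.** **The plan's own figures.** The point rests on none of them and changes none. For 30% versus 40% completion at two-sided alpha 0.05 and 80% power, the continuity-corrected two-proportion formula gives 376 per arm, as stated (356 without the correction). 376/0.30 = 1253.3, rounded up to 1254 consenters. The plan thus expects 1254 − 376 = 878 of 1254 consenters (70%) not to complete. Apart from formal withdrawals, these are all PI, so the rule for PI governs most of the response numerator.

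**Tracing one person through both arms.** Take someone who is willing when first spoken to and silently drops on meeting the IVR, before any NCD question.

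| | Human introduction | IVR introduction |
|---|---|---|
| Consent recorded before the drop? | Yes, spoken | No |
| Disposition | PI | R or NC |
| In response numerator? | Yes | No |
| In response denominator? | Yes | Yes |
| In completion denominator? | Yes | Yes if R, no if NC |

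**Illustration.** The documents give no loss rate, so every input here is assumed. Each arm has 2000 people in CI+PI+R+NC: 1200 willing (60%), 600 refusals and 200 non-contacts. Each arm yields 360 completes. A share t of the willing drops on meeting the IVR, and behaviour is identical in both arms.

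- Human arm response = 1200/2000 = 60.0% for every t.
- IVR arm response = 1200(1 − t)/2000.
- Spurious gap = 0.60t.

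| t | Human response | IVR response | Gap (points) | Response if one NCD answer is required, either arm |
|---|---|---|---|---|
| 0 | 60.0% | 60.0% | 0 | 60.0% |
| 5% | 60.0% | 57.0% | 3 | 57.0% |
| 10% | 60.0% | 54.0% | 6 | 54.0% |
| 20% | 60.0% | 48.0% | 12 | 48.0% |

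**Completion in the same example.** The human arm stays at 360/1800 = 20.0%. If the IVR arm's losses are coded R, it is also 360/1800 = 20.0%. If they are coded NC, they leave the denominator:

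- t = 5%: 360/1740 = 20.7%
- t = 10%: 360/1680 = 21.4%
- t = 20%: 360/1560 = 23.1%

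Completes over everyone in CI+PI+R+NC are 360/2000 = 18.0% in both arms, whichever code is used.

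**The case against.** The strongest reply is that microtrials 1 to 6 are sized on completion, not response. A person lost at transfer stays in the human arm's completion denominator, so that metric is not inflated, and a response gain without a completion gain would be visible. Partial surveys are also tabulated by question number, and Table 2 lists attrition by question as an outcome of microtrial 5, so people who stop before the first question could be found. This lowers the stakes but does not cure the problem. Response is still a named outcome tested by arm, and completion can move the other way when the IVR arm's early losses are coded NC. In that case identical behaviour yields two outcomes pointing in opposite directions.

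A second reply is that a human obtaining more agreement is the intervention working. That stands. Only those who agreed and then answered nothing are the artefact.

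A reader might infer more than the documents support:

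- **That the PI rule contradicts the account of non-initiated surveys before Figure 3.** It does not. That text lists hanging up before consent among surveys not initiated, which is the same threshold as PI. The stricter wording on initiation describes when the opt-out keys become available. It is a usable milestone, not a competing disposition rule.
- **That the artefact matches the 10-point difference the trial is sized for.** That difference is in completion, whereas the artefact is in response and its size is unknown.
- **That microtrial 7 has the same flaw.** A CATI operator goes on to ask the questions, so there is no transfer at which to lose people. Spoken versus keypad consent there is part of the modality under test.
- **That the artefact would decide the introduction used in microtrial 6.** The Microtrial #6 description draws the introduction from microtrials 4 and 5, but the Table 2 note draws on microtrials 1 to 4 only. The two need reconciling, and neither makes response the sole criterion.

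**Conclusion.** The point holds for one outcome in one microtrial. As defined, microtrial 5's response rate compares different milestones and favours the human introduction whenever some people agree to the operator and then silently drop before answering anything. The direction follows from the definitions. The size cannot be read from the documents: it is zero with no such loss and 3 to 12 points under the assumed 5% to 20% loss with 60% willing. The illustration also assumes that the same share would be lost on meeting the IVR in either arm. It does not follow that the whole of an observed human-arm advantage would be spurious, or that the sample size is affected.

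**What to change.** In section C.4, define PI for every arm as a respondent who was screened, consented and answered at least one NCD question; formal withdrawals stay R. Add a separate disposition, 'consented, not started' (CNS), for those who consented and answered none without formally withdrawing. Then:

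- Response = (CI+PI)/(CI+PI+CNS+R+NC).
- Completion = CI/(CI+PI+CNS+R).
- For microtrial 5, report consent and transfer loss by arm, so that the genuine effect on agreement is kept and shown separately.
- For microtrial 5, also report CI/(CI+PI+CNS+R+NC). Changing PI alone leaves completion sensitive to whether IVR-arm losses are R or NC; this ratio does not depend on that choice.

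The cost is one changed definition, one extra code and one extra ratio, from system logs and question-level tabulations the plan already uses. Reported response rates will fall slightly. The change should be made before microtrial 5 starts.

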The notification SMS will be sent before and on the same day on which the MPS will be sent. As discussed above, the exact timing of the notification SMS will be guided by the focus group discussions. Due to possible country specific mobile network problems, at a minimum, the SMS will be sent at least one hour before the MPS is sent; therefore ensuring the SMS reaches the participant before the IVR survey is sent. After the notification SMS is sent, the MPS will be sent to the same randomly generated mobile phone number. When a randomly dialed number is connected (i.e. a respondent picks up the phone), the respondent will be presented with a brief pre-recorded introduction to the study and provided an opportunity to select the survey’s language (except for *microtrial #5;* details provided below*)*. An example of the narrated introduction and language selection is, “Hello, its [Name] from the [Implementing Agency]. Earlier today, we sent you a text message about participating in a mobile phone survey.” After hearing the introduction, participants will be asked to select their preferred language for which the IVR survey will be narrated, “Please pick a language to continue hearing the survey instructions [and how you could qualify for free airtime (if countries are using airtime incentive] Press 1 to continue in [Language X] Press 2 to continue in [Language Y]” The results of the FGD (JHU IRB No: 0000709) will assist in the selection of the exact wording for the introduction and language selection.

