The potential survey outcomes are depicted in figure 3. In a large proportion of the randomly selected mobile phone numbers, the randomly dialed mobile phone number may not exist, participants may refuse to participate in the MPS, or the mobile phone number may be valid, but the IVR survey was not initiated. Reasons for this latter category include, (1) phone was turned off or out of battery, (2) mobile phone was out of network coverage area, and (3) personal reasons, which include not hearing the mobile phone ring or respondent hanging up before consenting to the study. In these instances where the MPS was not initiated by a respondent, no future call back attempts to enroll participant will be made. Moreover, for respondents who initiate the IVR survey, but do not complete it (labeled an ‘incomplete survey’ in the figure), no call back attempts to re-initiate the survey will be made. Note, that as described in the sample size section, a sub-sample of participants (n=30) will be called back by a human interviewer to ask why they did not complete the survey. Unlike traditional household surveys, multiple attempts to achieve participant response are not needed since the selection of mobile phone numbers and timing of delivery are both random, thereby reducing the potential for non-response bias, but also because of the very large pool of possible respondents in the sampling set of all mobile phone owners.

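### The contact rate scores people who picked up but did not engage as not contacted, so an arm can change it after the phone has been answered, most clearly in microtrial 4

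*Protocol*

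**What the plan says.** All of the definitions stand in section V.C, item 4 of the protocol (data analysis plan).

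- Contact rate = (CI+PI+R) / (CI+PI+R+NC+U).
- NC, labelled non-contact, is "a working phone number where the respondent picked up but did not engage with the survey". On how it is recognised, the plan adds: "This is assessed by looking at the system log for time spent on the survey". It gives no time threshold.
- U takes numbers whose working status cannot be settled, and this includes calls that nobody answered.
- PI is "a respondent who consented to the survey but did not answer all questions". R is "a respondent who: 1) did not consent to the survey, or 2) formally withdrew during the survey". Both are in the numerator.

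The same item has contact, response and completion compared by arm in each microtrial, with alpha 0.05. Table 2 lists the contact rate as an outcome of all seven microtrials, and the descriptions of microtrials 2 and 4 name it in their aims.

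On the order of events, Survey Delivery says: "When a randomly dialed number is connected (i.e. a respondent picks up the phone), the respondent will be presented with a brief pre-recorded introduction". The same section lists reasons why a survey was not initiated. Beside phones that are off or out of coverage, it gives personal reasons, among them "not hearing the mobile phone ring or respondent hanging up before consenting to the study".

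**The concern.** The label and the definition of NC disagree. A person in NC answered the phone, yet the formula scores that person like a number that rang unanswered or does not exist. A person who answered and declined counts as contacted.

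The rate therefore combines two things: whether the phone was answered, and whether the person stayed long enough to engage. An arm that acts only after pick-up can change the second and so produce a difference in contact. In microtrial 4 the arms share the same incentive and differ only in introduction content and voice. Pick-up there can differ only by chance. A significant contact difference would reflect early drop-out, but under its present name it could be reported as better success in reaching phones.

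**Working it through.** The protocol states no contact rate, so there is no figure to reproduce. The check applies its formula.

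**Algebra.** Let N = CI+PI+R+NC+U, pick-up P = (CI+PI+R+NC)/N, and early drop-out h = NC/(CI+PI+R+NC). Then

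contact as written = (CI+PI+R)/N = P × (1 − h).

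Two arms with equal P have equal contact only if h is also equal.

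**Inputs (assumed, as the protocol gives none).** 10,000 numbers per arm; pick-up 30% in both; h = 50% in arm A and 40% in arm B. Age-ineligible respondents, whom the protocol removes from the formulas, are left out.

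| | CI | PI | R | NC | U | Contact as written | With NC in numerator |
|---|---|---|---|---|---|---|---|
| A | 376 | 878 | 246 | 1,500 | 7,000 | 1,500/10,000 = 15.0% | 3,000/10,000 = 30.0% |
| B | 451 | 1,054 | 295 | 1,200 | 7,000 | 1,800/10,000 = 18.0% | 3,000/10,000 = 30.0% |

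The pooled proportion is 3,300/20,000 = 0.165. The standard error is √(2 × 0.165 × 0.835/10,000) = 0.00525, so z = 0.03/0.00525 = 5.72 and two-sided p is about 1e-8, although pick-up is identical.

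The response rate, which already has NC in its denominator, is 1,254/3,000 = 41.8% against 1,505/3,000 = 50.2%. The completion rate is 25.1% in both arms (376/1,500 and 451/1,800).

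**Range (pick-up equal in both arms throughout).**

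| Numbers per arm | Pick-up | Early drop-out | Contact as written | Result |
|---|---|---|---|---|
| any | any | equal | equal | no difference |
| 5,000 | 20% | 50% v 45% | 10.0% v 11.0% | p = 0.10 |
| 10,000 | 20% | 50% v 45% | 10.0% v 11.0% | p = 0.02 |
| 5,000 | 30% | 50% v 45% | 15.0% v 16.5% | p = 0.04 |
| 5,000 | 50% | 50% v 45% | 25.0% v 27.5% | p = 0.0045 |
| 5,000 | 40% | 60% v 40% | 16.0% v 24.0% | z = 10 |

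**Coding of exits before consent.** Survey Delivery groups hanging up before consent with unreachable phones, while the first limb of R (did not consent) could also cover it. If 500 of arm A's 1,500 NC cases were coded R instead, contact as written would move from 1,500/10,000 = 15.0% to 2,000/10,000 = 20.0%, and completion from 376/1,500 = 25.1% to 376/2,000 = 18.8%. With NC in the numerator, contact stays at 30.0% under either coding.

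**The case against.** The best defence is that the authors mean contact as reached and engaged. Survey Delivery treats hanging up before consent as a survey not initiated, and microtrial 4 asks whether introduction and voice affect contact, which makes sense only if engagement is part of it. The definitions are printed, so a careful reader is not misled. The rates are said to be adapted from a published standard, and departure from a source not at hand cannot be asserted.

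Little depends on the rate. Primary Objectives 1 and 2 name response, completion and refusal. The sample size for microtrials 1 to 6 rests on completion. The incentive is carried forward on response and completion, and the choice of introduction for microtrial 6 refers to top performance without naming a rate. Early drop-out already lowers the response rate, and every count needed for a pick-up rate is already required by the planned formulas.

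The points about consequence stand and limit the weight of the finding. The reading of contact as engagement explains the formula but leaves the conflict in place: a group defined by having picked up is labelled and scored as not contacted. If engagement is what is wanted, the measure needs a name that says so.

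**Conclusion.** The concern holds in limited form. The contact rate as written is a pick-up-and-engage rate, and an arm can change it after pick-up. Microtrial 4 is the clear case. The size rests entirely on assumed pick-up and drop-out rates: from no difference when early drop-out is equal, through p = 0.10 for a small contrast, to z = 10 for a large one. The consequence is confined to the reporting and interpretation of a listed outcome.

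A reader might infer more, and the protocol does not support it:

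- That everyone who answers and then hangs up is scored as not contacted. Drop-outs after consent are PI, and some exits before consent may be R; both count as contacted.
- That the rate measures hang-ups instead of contact. U is also in the denominator, so real differences in pick-up still enter. In microtrial 2, part of the airtime reaches the phone before the call in one arm, so pick-up itself may differ.
- That arms with equal pick-up must differ. They do so only if early drop-out differs.
- That microtrial 5 is as clear as microtrial 4. There an operator places the call in one arm, and equal pick-up is not assured.

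**What to change.** In section V.C, item 4:

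1. Define contact rate = (CI+PI+R+NC) / (CI+PI+R+NC+U).
2. Report early drop-out, NC / (CI+PI+R+NC), by arm.
3. Keep the present formula, if wanted, under an accurate name such as *pick-up-and-engage rate*.
4. State that contact in microtrial 4 is a balance check and not an effect of the introduction. The effect of the introduction would then be read from early drop-out, response and completion.
5. Reconcile the definitions of NC and the first limb of R with Survey Delivery, and state the log-time rule that separates the two codes. Changing the contact formula does not settle this, and the completion rate depends on it.

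The cost is one extra tabulated row and the loss of contact as an effect outcome in microtrial 4. The response and completion formulas stay as they are, and no new data are needed. The corrected rate can still shift slightly by arm, because under-18s are removed only once they have reported their age; a footnote is enough for that.
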